## Abstract

**Introduction:**

Septic shock, a life-threatening condition, can result in cerebral dysfunction and heightened mortality rates. In these patients, disturbances in cerebral hemodynamics, as reflected by impairment of myogenic cerebral autoregulation (CA), metabolic regulation, expressed by critical closing pressure (CrCP) and reductions in intracranial compliance (ICC), can adversely impact septic shock outcomes. The general recommendation is to maintain a target mean arterial pressure (MAP) of 65 mmHg but the effect of different MAP targets on cerebral hemodynamics in these patients is not clear and optimal targets might be dependent on the status of CA. This protocol aims to assess the cerebral hemodynamics profile at different pressure targets in septic shock patients.

**Methods:**

Prospective, non-randomized, single-center trial, which will study cerebral hemodynamics in patients with septic shock within 48 hours of its onset. Patients will be studied at their baseline MAP and at three MAP targets (T1: 65, T2: 75, T3: 85 mmHg). Cerebral hemodynamics will be assessed by transcranial Doppler (TCD) and a skull micro-deformation sensor (B4C). Dynamic CA will be expressed by the autoregulation index (ARI), calculated by transfer function analysis, using fluctuations of MAP as input and corresponding oscillations in cerebral blood velocity (CBv). The instantaneous relationship between arterial blood pressure and CBv will be used to estimate CrCP and resistance-area product (RAP) for each cardiac cycle using the first harmonic method. The B4C will access ICC by intracranial pressure waveforms (P2/P1). The primary aim is to assess cerebral hemodynamics (ARI, CrCP, RAP, and P2/P1) at different targets of MAP in septic shock patients. Our secondary objective is to assess cerebral hemodynamics at 65mmHg (target recommended by guidelines). In addition, we will assess the correlation between markers of organ dysfunction (such as lactate levels, vasoactive drugs usage, SOFA score, and delirium) and CA.

**Ethics and dissemination:**

The results of this study may help to understand the effect of the recommended MAP and variations in blood pressure in patients with septic shock and impaired CA and ICC. Furthermore, the results can assist large trials in establishing new hypotheses about neurological management in this group of patients. Approval was obtained from the local Ethics Committee (28134720.1.0000.0048). It is anticipated that the results of this study will be presented at national and international conferences and will be published in peer-reviewed journals in 2024 and 2025.

**Trial registration:**

**Trial registration number:**
NCT05833607. https://clinicaltrials.gov/study/NCT05833607.

## Introduction

Cerebral dysfunction in sepsis, spanning delirium to coma, is closely linked to elevated mortality rates [1,2]. The underlying pathophysiological alterations contributing to patient deterioration and death are complex and multifaceted. Nevertheless, several studies have highlighted an association between altered cerebral hemodynamics and the onset of sepsis and shock [3–5].

Recent findings indicate that patients with septic shock exhibit compromised dynamic cerebral autoregulation (dCA) [3,4]. A reduced autoregulation index (ARI)relative to healthy individuals also showed an inverse correlation between the Sequential Organ Failure Assessment (SOFA) score Another observational trial with 100 patients using the mean velocity index also demonstrated an association between brain dysfunction, sepsis, and impairment of dCA [4].

DCA characterizes the brain’s ability to maintain consistent cerebral blood flow (CBF), notwithstanding variations in mean arterial pressure (MAP) [6]. This capability acts as a protective mechanism, shielding the brain tissue from extremes of CBF changes and the associated risks of both hyperperfusion and hypoperfusion due to MAP fluctuations [7].

Patients with sepsis are susceptible not only to dCA impairments but also to elevated intracranial pressure (ICP) and brain edema [8]. Such pathophysiological shifts result in decreased intracranial compliance (ICC), exacerbating the already compromised dCA. Deterioration of cerebral perfusion can also be reflected by changes in critical closing pressure (CrCP), which represents the arterial blood pressure level at which CBF reaches zero [9], and resistance-area product (RAP), which represents the slope of the instantaneous pressure–velocity relationship for each cardiac cycle [10]. Alterations in CrCP can reflect disturbances in metabolic CBF control and have serious deleterious effects on cerebral perfusion by leading to hyper or hypoperfusion [10,11].

While current guidelines from the Surviving Sepsis Campaign advocate for a target MAP of 65 mmHg to secure tissue perfusion [12], the empirical basis for this MAP threshold is scant. This is primarily due to the limited research into cerebral hemodynamic dysfunction in septic patients, highlighting a significant gap in our understanding. Some trials have sought to establish an association between systemic and cerebral factors. Masse et al. did not find different measures of CBF in septic patients when comparing those who used vasoactive drugs to those who did not, indicating that MAP is not the sole contributing factor in ensuring CBF [13]. Another study, in which dobutamine was infused during transcranial Doppler (TCD) monitoring, suggests that dobutamine increases CBF but not cerebral oxygen consumption (estimated by jugular bulb oximetry) in stable septic patients [14]. It is important to highlight that these studies did not evaluate either the dCA or ICC of their patients.

Considering the profile of critically ill patients, the use of multimodal monitoring has been increasingly recommended, especially with non-invasive tools, leading to new diagnostic hypotheses and interventions [14]. A validated non-invasive mechanical sensor (B4C) has been shown to effectively capture crucial aspects of the intracranial pressure waveform [15,16]. In a recent study, the B4C sensor was employed to predict intracranial pressure elevations with a high degree of accuracy, demonstrating comparable results to those obtained from invasive monitoring techniques [17]. Therefore, this tool has considerable potential for the management of critically ill patients undergoing multimodal, non-invasive monitoring.

In this pilot study, we aim to investigate the impact of varying MAP targets on cerebral hemodynamic parameters, utilizing non-invasive methodologies such as TCD and the B4C sensor.

## Objectives

Our primary endpoint is to evaluate the effect of various mean arterial pressure (MAP) targets on cerebral hemodynamics (ARI, CrCP, RAP, and P2/P1) in patients with septic shock. Our secondary endpoint is to assess cerebral hemodynamics at 65 mmHg and its correlation with indicators of clinical severity and neurological dysfunction.

We hypothesize that these results will present a different pattern in patients with impaired dCA and altered ICC and consider whether these parameters can be modified by different MAP levels, suggesting a personalized approach to cerebral hemodynamics.

## Trial design

We will perform a single-center prospective study with consecutive inclusion of patients with septic shock within 48 hours of its onset.

## Methods: Participants, interventions, and outcomes

### Study setting

This single-center clinical trial, a non-randomized study, will be conducted in three intensive care units (ICUs) at Hospital São Rafael, Brazil. A screening by a multidisciplinary team will be carried out daily to identify candidates successively for inclusion, and then the inclusion and exclusion criteria will be applied.

Data collection is expected to take one year and to include at least 40 patients. Measurements will be performed using Transcranial Doppler (TCD; DWL Doppler box, Germany, Serial number: DB-1964) with a 2 MHz probe, B4C (Brain4care Corp., São Carlos, Brazil), and capturing data from the multiparametric monitor (Fig 1). Clinical and laboratory data will be collected from all subjects.

**Fig 1 pone.0304412.g001:**
[figure not shown]
Cerebral monitoring for data collection of the study. 1) Transcranial Doppler probe maintained in position with a probe-holder; 2) Brain4care sensor; 3) Brain4care main display showing the cerebral compliance curve; 4) Transcranial Doppler device main display showing cerebral blood velocity of the middle cerebral artery. (Under a CC BY license, with permission from [name]. [name], original copyright 2023).

The clinical trial study protocol was approved by the local Ethics Committee (28134720.1.0000.0048) and in Clinicatrials.gov (NCT05833607).

#### Selection criteria

Study enrollment will include patients experiencing septic shock for up to 48 hours and still necessitating vasopressor support. Detailed inclusion and exclusion criteria are provided in Table 1.

**Table 1 pone.0304412.t001:** Selection criteria.

Inclusion criteria	Exclusion criteria
• Age > 18	• No temporal window for TCD
• Septic shock < 48h • The timing will be counted from ICU admission or the start of noradrenaline infusion for patients already in critical care units.	• Hepatic or uremic encephalopathy
	• Pregnancy
	• Acute or prior neurological insult*
	• Exogenous intoxication
	• Dementia**
	• Severe hypercapnia*** • Instability for acute arrhythmia
	• Extracorporeal support device by modifying the pulse waveform****
	• Extreme severity, with imminent risk of death

* Ischemic or hemorrhagic stroke, aneurysm, arteriovenous malformation, hydrocephalus, neurological surgery, central nervous system infection.

** Reported or written in medical records.

*** Partial pressure of arterial carbon dioxide (PaCO2) > 65mmHg.

**** Intra-aortic balloon pump (IABP) and Extracorporeal membrane oxygenation (ECMO).

#### Who will take informed consent?

Local investigators will present the study details to either the patient or their legal representatives, such as next of kin or legal guardians, covering all crucial trial aspects. This will ensure that a comprehensive and informed discussion takes place, facilitating a clear understanding of the study’s scope and procedures.

### Study outcome

The primary endpoint is to assess the impact of different MAP targets on cerebral hemodynamics (ARI, CrCP, RAP by TCD, and P2/P1 by B4C) in patients with septic shock.

Secondary objectives: (1) Evaluate the effects of targeting a MAP of 65 mmHg on cerebral hemodynamics in patients with septic shock. (2) Evaluate the correlation between ARI and B4C. (3) Correlate criteria of clinical severity and neurological dysfunction with cerebral hemodynamics (This will involve assessing the correlation between markers of organ dysfunction such as lactate levels, usage of vasoactive drugs, Sequential Organ Failure Assessment (SOFA) score, and delirium with CA). (4) Assess 28-day mortality.

### Participant timeline

The participant timeline is reported in Fig 2.

**Fig 2 pone.0304412.g002:**
[figure not shown]
Flowchart: MCA, middle cerebral artery; TCD, transcranial Doppler; B4C, brain4care; ARI, autoregulation index; CA, cerebral autoregulation; Crcp, critical closing pressure; RAP, resistance-area product.

### Sample size

This pilot project is designed to elucidate the physiological changes correlated with different blood pressure targets within cerebral hemodynamics. The insights gained will facilitate the determination of sample sizes for subsequent studies following this protocol.

### Recruitment

The recruitment phase is set from July 2023 to June 2025. Table 2 details the project’s steps. Septic shock patients starting on noradrenaline, whether newly admitted to or already in the ICU, are potential candidates. However, if an alternative diagnosis emerges within 48 hours, they will be removed from the candidate pool. The multiprofessional team will daily inform the research group about new vasopressor requirements, ensuring rigorous monitoring.

**Table 2 pone.0304412.t002:** Protocol chronology.

		STUDY PERIOD					
	Recruitment	Allocation	Intervention protocol (5 min on each MAP target)			Clinical outcome	
	*07/23–06/25*	*< 48 hours ICU admission*	*MAP 65 mmHg*	*MAP 75 mmHg*	*MAP 85 mmHg*	*7*^*th*^ *day*	*28*^*th*^ *day*
**ENROLMENT:** **Eligibility screen** **Informed consent** **Allocation**							
	x						
	x						
		x					
							
**INTERVENTIONS:** ** *Induce different MAP targets* ** ** *Monitor bilateral MCA by TCD and B4C* **							
			x	x	x		
			x	x	x		
							
** *ASSESSMENTS* **							
**Sex, age, time, time since admission to the ICU, infection site, comorbidities, APACHE, SOFA, vasopressor dosage, blood analysis**		x					
**TCD: ARI, CrCP, RAP**			X	X	X		
**B4C: P2/P1 ratio**			X	X	X		
**Brain dysfunction**		X				x	x
**Ventilation free days**							x

MAP: Mean arterial pressure, MCA: Middle cerebral artery, TCD: Transcranial doppler, B4C: Brain4care, ICU: Intensive care unit, APACHE: Acute Physiologic and Chronic Health Evaluation, SOFA: Sequential Organ Failure Assessment, ARI: Autoregulation index CrCP: Critical closing pressure, RAP: Resistance-area product.

The locals researchers will be designated for daily data collection and interactions with patients or their families after the, ensuring that recruitment is possible within 48 hours from the onset of vasopressor therapy to optimize data gathering.

## Methods: Assignment of intervention

### Sequence generation

All patients using vasoactive drugs will be considered for inclusion in the clinical trial, subject to the application of inclusion and exclusion criteria (Table 2).

### Concealment mechanism

Given the population to be studied, the absence of a control group or the use of placebo, means that concealment is not appropriate for the study.

### Assignment of interventions: Who will be blinded?

This study will analyze the parameters of cerebral hemodynamics after data collection. Therefore, during data acquisition, it is necessary to assess the quality of hemodynamic recordings. However, the final data, involving derived parameters, will not be obtained simultaneously. Patients will be identified by numbers in the database, ensuring that the analysis remains uninfluenced by the researcher. Consequently, no additional blinding will be implemented.

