## Methods: Data collection and management

Data collection on admission will include the following: demographic characteristics, comorbidities, source of infection, Sequential Organ Failure Assessment at ICU admission, temperature, hemogram lactate, hepatic and renal markers, Glasgow Coma scale or Richmond Agitation Sedation Scale, Confusion Assessment Method for the ICU scale, drug for sedation, neuromuscular blocking agents, mechanical ventilation, quantify vasoactive drug dose on collection day, arterial blood gasses before and after the protocol, presence of acute cardiac dysfunction by echocardiography and left ventricle ejection fraction. We will describe the utilization of antipsychotics or sleep-improving medications before ICU admission.

At the time of data collection, the presence of brain dysfunction associated with sepsis will be assessed by: a Glasgow scale score < 15 or when disorientation, disorganized thinking, or agitation are reported by the attending physician, regardless of sedative/analgesic use and in the absence of neurological disease (i.e., dementia, cerebrovascular disease, brain tumors, previous traumatic brain injury). Data from medical records will be used to access such information, the description of the change in the level of consciousness or the use of antipsychotics or dexmedetomidine will be interpreted as a brain dysfunction.

Systemic physiological monitoring will be performed by an arterial line, cardioscopy, pulse oximetry, and capnography (if unavailable at the time of collection, this will be described). Before starting the monitoring, the proper functioning of the arterial line will be confirmed and the site described.

Each patient will adhere to a uniform protocol where, after establishing baseline measures, the mean arterial pressure (MAP) targets will be sequentially increased in the order of 65, 75, and then 85 mmHg. This structured approach ensures sample homogeneity.

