CA assessment by TCD will use a 2 MHz probe, supported by a helmet frame, the middle cerebral artery will be located through the window of the temporal bone, then it will be confirmed by depth and waveform, and one of the sides will be chosen and will be kept during the protocol. All hemodynamic parameters will be collected simultaneously and transmitted to the Doppler Box through a cable connected to the multiparameter monitor. A B4C sensor will be placed on the contralateral temporal window, which consists of a monitor that quantifies local cranial bone deformations using strain-gauge sensors. The system will be positioned on the frontotemporal region, approximately 3 cm over the first third of the orbitomeatal line, and the software will indicate the wave quality generated. The measurement of ICC will be done using the curve generated by B4C, and P2/P1 > 1 will be considered altered. The quality of measurements will be closely monitored during the duration of recordings to ascertain their acceptability for subsequent stages of off-line analysis.

The instantaneous relationship between arterial blood pressure and CBv will be used to estimate CrCP and RAP for each cardiac cycle using the first harmonic method [18]. Beat-to-beat data will be spline interpolated and resampled at 5 Hz to produce signals with a uniform time base.

Dynamic CA will be assessed using transfer function analysis, using spontaneous fluctuations of MAP as input and corresponding changes in CBv as output in recordings for each MAP target (lasting 5 min), as described previously [19,20]. The Welch method will be adopted for smoothing spectral estimates obtained with the fast Fourier transform (102.4 s segments, 50% superposition) leading to frequency-dependent estimates of coherence, gain and phase. Using the inverse fast Fourier transform, the CBv response to a step change in MAP will also be derived and compared with ten template curves proposed by Tiecks et al. [21] to estimate the ARI [22,23] Baseline cerebral hemodynamic parameters will be reported as the average over a 5-min recording at rest. Values of ARI < 4 will characterize impaired dCA.

The protocol will be interrupted if at any time during the data collection any of the adverse effects, described below, are identified.

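### Numbering patients does not conceal the MAP target, so it cannot support the claim that the analysis is uninfluenced or the decision to add no further blinding

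*Protocol article*

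**What the plan says.** All references are to the protocol article.

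- **Assignment of interventions: Who will be blinded?** gives two safeguards. The first is timing: "However, the final data, involving derived parameters, will not be obtained simultaneously". The second is coding: "Patients will be identified by numbers in the database, ensuring that the analysis remains uninfluenced by the researcher". The section then concludes: "Consequently, no additional blinding will be implemented".
- **Methods: Data collection and management** fixes one order for every patient; after baseline, the "targets will be sequentially increased in the order of 65, 75, and then 85 mmHg". On recording quality it says: "The quality of measurements will be closely monitored during the duration of recordings to ascertain their acceptability for subsequent stages of off-line analysis". On the B4C endpoint it says: "The measurement of ICC will be done using the curve generated by B4C, and P2/P1 > 1 will be considered altered". It adds that the B4C software gives an indication of wave quality.
- **Fig 1 (caption)** lists two bedside displays: "Brain4care main display showing the cerebral compliance curve" and "Transcranial Doppler device main display showing cerebral blood velocity of the middle cerebral artery".
- **Statistical methods: Outcomes** compares the primary parameters across T0 (basal), T1, T2 and T3 by repeated-measures methods.
- **The subsection on non-adherence and missing data** removes a patient whose TCD recording is considered to be of inadequate quality, and fills missing data with the mean of what is available.

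**The concern.** Blinding an assessment is useful when it hides the factor being compared. Here that factor is the MAP level, and each patient serves as their own comparison. Identity does not vary across the contrast, so concealing it gives the contrast no protection. The article nevertheless treats numbering as enough to keep the analysis free of influence and draws a design decision from it.

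The step left exposed is the acceptance of recordings. If the decision to keep a recording depends on the target together with some impression of the outcome, the retained data are a selected sample, and the estimated effect of MAP target on ARI, CrCP, RAP or P2/P1 can move without any physiological cause.

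**Working it through.** The article gives no figure on this point, so there is nothing of its own to reproduce. The check has two parts.

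**Part 1: the statements side by side**

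1. *Does numbering hide the target?* No. A patient code is the same at T0, T1, T2 and T3. The order 65, 75, 85 mmHg is identical for everyone, so the target is known at each step.
2. *Is acceptability judged with the target known?* Yes for the bedside step, since quality is assessed while recordings run. The TCD exclusion rule rests on judgement. The article does not say when that exclusion is made, but describes nothing that would hide the target at a later stage.
3. *Is the outcome known at that moment?*
   - ARI, CrCP and RAP: no. They are computed off-line, and the TCD display shows velocity only.
   - P2/P1: in part. It is read from the B4C curve, which is on display. The article does not say that the numerical ratio is shown.
4. *Is the decision subjective?* Clearly for TCD. Less so for B4C, where software indicates wave quality and no rejection rule is stated.

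The timing safeguard therefore covers three of the four primary parameters well and the fourth only partly. The coding safeguard covers none of them for the comparison that matters.

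**Part 2: how large could selection bias be?**

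Inputs:
- n = 40, from Study setting (the stated minimum).
- Within-patient correlation between two targets, ρ = 0.7: an assumption, not in the article.
- Proportion rejected, p = 5%, 10% or 20%: an assumption, not in the article.
- Normal outcome with SD 1 at each target, and rejection of exactly the lowest p at one target: a worst-case assumption.

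Formulas:
- Shift of the mean at that target: φ(z_p)/(1 − p).
- Patients are excluded whole, as the article's TCD rule says, so the other target's mean moves by ρ times that amount. Shift of the paired contrast: (1 − ρ) × φ(z_p)/(1 − p).
- SE of the paired contrast: √[2(1 − ρ)/n] = √(2 × 0.3/40) = √0.015 = 0.122 SD, holding n at 40.

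| Rejected | Shift at one target (SD) | Contrast shift, whole patient excluded (SD) | In SE units |
|---|---|---|---|
| 5% | 0.109 | 0.3 × 0.109 = 0.033 | 0.27 |
| 10% | 0.195 | 0.3 × 0.195 = 0.059 | 0.48 |
| 20% | 0.350 | 0.3 × 0.350 = 0.105 | 0.86 |

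If a single-target recording were dropped instead, and its value replaced by the mean of the remaining values at that target (one possible reading of the imputation rule), the shift in the second column would pass in full to the contrast: 0.109/0.122, 0.195/0.122 and 0.350/0.122, or about 0.9, 1.6 and 2.9 SE. The imputed values would also shrink the apparent variance. The stated TCD rule does not work this way, and no B4C rejection rule is given.

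**The case against.** The case for leaving the text alone has real force.

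- *The section does not rest on numbering alone.* Deriving parameters after collection is a genuine safeguard. ARI needs transfer function analysis and template fitting, and CrCP and RAP need the first harmonic method. Nobody can read these from a velocity trace. This stands for the TCD parameters. It does not extend fully to P2/P1, and it does not rescue the claim made for numbering.
- *The bedside team must know the target in order to set it.* True. The remedy therefore belongs in the off-line step.
- *Quality criteria and export procedures are commonly left to a fuller document.* Also true, and their absence from the article is not held against it. What is at issue is an assurance that the article does state.
- *This is an uncontrolled pilot with mostly algorithmic endpoints.* This limits the consequences but does not make the inference valid.

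A reader might infer something stronger: that recordings are accepted or rejected in knowledge of both target and result. The documents do not support that. Three of the four parameters are unknown at the bedside. For the fourth, the curve is visible but its quality is flagged by software. The only stated rejection rule concerns TCD, where the result is not visible; the visible curve is B4C, where no rejection rule is stated. Nor does the article say that the same people judge acceptability a second time off-line, that recordings are repeated, or that a particular direction of change is expected. The Objectives ask whether the parameters can be modified by MAP level, without giving a direction.

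**Conclusion.** The assurance does not hold as written. Numbering conceals identity and not MAP target, so it cannot keep the within-patient comparison uninfluenced, and the conclusion that no more blinding is needed does not follow from it. Later derivation of the parameters is a partial safeguard: good for ARI, CrCP and RAP, weaker for P2/P1.

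The documents do not show that any bias will occur or how large it would be. Under whole-patient exclusion, the contrast would move by about 0.03 to 0.11 SD, or 0.3 to 0.9 SE, if 5% to 20% were rejected strictly on the outcome at one target, with n = 40 and an assumed correlation of 0.7. Weaker dependence on the outcome gives less, and a lower correlation gives a larger shift in SD. Rejection that followed the difference between two targets is outside this bound, but it would require the derived values at both to be known. The larger figures of 0.9 to 2.9 SE may be tempting to cite, but they need single-target rejection with mean imputation, which is not the stated TCD rule.

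This is a correction to a stated safeguard, with a cheap improvement attached. It is not evidence that the primary analysis is invalid.

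**What to change.** Replace the sentence on patient numbering, and the conclusion drawn from it, with text to this effect:

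1. Bedside staff are not blinded to the MAP target.
2. For the off-line quality step, each recording is exported under a random code, without patient number or target label and in shuffled order. Where feasible, the pressure trace is shown with its mean removed.
3. Acceptance or rejection is decided on signal-quality criteria fixed in advance, for TCD and B4C alike, and locked before ARI, CrCP, RAP and P2/P1 are computed.
4. The number of recordings rejected is reported for each of T0 to T3.

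The cost is a relabelling step and a change in the order of work. No extra patients or staff are needed. Masking will be imperfect, because MAP is an input to the signals and its level may sometimes be recognisable. Locking the decision before derivation still works in that case, and the per-target counts let readers see whether rejection was uneven.
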